### Outcome measures

#### Primary outcome measure

The difference in any change in fasting plasma glucose level between the intervention and placebo groups between baseline and 12 weeks.

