### Data analysis and statistical considerations

#### Sample size

As this is a pilot study, no evidence about blood glucose differences is available for this product. Therefore, it was decided to use the number of participants needed to detect a mean difference between the groups in fasting plasma glucose level of 2.0 mmol/l (standard deviation 2.0 mmol/l) at week 12 with 80% power and 95% confidence as a starting point. The number of subjects needed is 32. The fact that the study includes two different cohorts (participants with prediabetes and early type 2 diabetes mellitus) was also taken into consideration, as owing to the lack of stratification at randomization the variance could be high. Therefore, the sample size has been inflated to 30 per group (including a drop-out rate of 25%) to give a total sample size of 60 eligible participants.

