#### Statistical analysis

Analysis will be conducted using the intention-to-treat principle and missing data will be imputed with baseline values for a conservative estimate (i.e. no change). Descriptive statistics will be presented as mean ± standard deviation, or median with range, as appropriate. Primary and secondary outcomes will be analyzed using generalized linear models. The following covariates will be added to the model: sex, age and percentage weight change. Additionally, if there is an imbalance between the groups of prediabetes and type 2 diabetes mellitus, this will be included as a covariate in the model. Three planned subgroup analyses will be completed between participants who are taking metformin, participants classified as prediabetic or type 2 diabetes mellitus and participants defined as compliant. Chi–square analysis will determine associations between categorical variables.

For the gut microbiome analysis, sequenced data will be interpreted using the bioinformatics tools programmed in the Ion Reporter™ software. Quantitative Insights Into Microbial Ecology (QIIME) algorithms will determine the bacterial diversity within a sample (alpha diversity) and between all the samples (beta diversity). Additionally, multivariate data analysis with principal component analysis on the diversity indexes and comparisons of genus and species level data will be performed to reveal differences in the microbial composition between the two groups. Differences in relative abundance of taxa between the intervention and placebo group and between participants receiving and not receiving metformin will be determined using ANOVA, using subject as a blocking factor. Changes in relative abundance will be tested for correlations with patient biochemical measurements. For all statistical tests, the Benjamini–Hochberg false discovery rate adjustment [20] will be used to account for the number of taxa tested in each comparison.

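### The covariate list for the change-from-baseline models omits each outcome's own baseline value, which costs precision and leaves a conditional residual of any chance baseline imbalance

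*Protocol article*

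**What the plan says.** The Primary outcome measure section defines the endpoint as "The difference in any change in fasting plasma glucose level between the intervention and placebo groups between baseline and 12 weeks". Under Statistical analysis, "Primary and secondary outcomes will be analyzed using generalized linear models", and the adjustment set follows: "The following covariates will be added to the model: sex, age and percentage weight change". One further term is conditional: "if there is an imbalance between the groups of prediabetes and type 2 diabetes mellitus, this will be included as a covariate in the model". The article nowhere names the baseline value of fasting glucose, or of any other outcome, as a covariate.

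Three other places bear on this. The Allocation section states that randomization is unstratified. The Sample size section recognises the consequence of mixing two glycaemic cohorts, saying that "owing to the lack of stratification at randomization the variance could be high". The Blood samples section has fasting blood drawn at baseline and at week 12, so the missing covariate will be in the database. Statistical analysis also replaces missing values with the baseline value, which sets the change to zero.

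**The concern.** Baseline glucose usually predicts its own later change: people who start high tend to fall, and people who start low tend to rise. The Inclusion criteria admit fasting glucose from 5.6 mmol/l on one prediabetes route and from 7.0 mmol/l, with no stated ceiling, on one diabetes route. A wide baseline spread is therefore likely. With 30 per arm and no stratification, the arms can start at noticeably different levels by chance.

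A change score removes baseline with a fixed slope of 1. If the true slope of week 12 on baseline is below 1, this over-corrects, and the arm that starts higher appears to improve more. Variance that baseline could explain also stays in the error term. The protocol answers its own worry about variance by enlarging the sample, and leaves unused a predictor it already measures. The same list serves the secondary change outcomes, such as HbA1c, lipids and hs-CRP.

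**Working it through.** **Inputs from the article (Sample size).** The trial is sized "to detect a mean difference between the groups in fasting plasma glucose level of 2.0 mmol/l (standard deviation 2.0 mmol/l) at week 12". Power is set at 80% and the confidence level at 95%, read as a two-sided 5% test. Before inflation, "The number of subjects needed is 32". The final size is 30 per arm, 60 in total, allowing for 25% drop-out.

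**Inputs assumed.** The correlation r between baseline and week-12 glucose is not given, so 0.3 to 0.9 is shown. The SD of 2.0 mmol/l is stated for week 12 and is assumed at baseline too. The formulas compare a model of change on treatment with and without baseline; the other covariates are ignored.

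**The plan's own figure.** Per arm, n = 2 × (1.96 + 0.842)² × (2.0/2.0)² = 15.7, rounded up to 16, or 32 in total. This matches. At 30 per arm, power for 2.0 mmol/l with SD 2.0 is about 97%.

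**Precision, complete data.** Let s be the common SD.
- Variance of the change without baseline: 2(1-r)s².
- Residual variance with baseline: (1-r²)s².
- Ratio, with over without: (1-r²) / [2(1-r)] = (1+r)/2.

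**Precision under the planned imputation.** Suppose a fraction p = 0.75 is observed, the rest have change set to zero, drop-out is unrelated to baseline, and mean change is near zero.
- Variance of the change: 2p(1-r)s².
- Covariance with baseline: -p(1-r)s².
- Ratio: 1 - p(1-r)/2.

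**Chance imbalance.** The SD of the baseline difference between arms is 2.0 × √(2/30) = 0.52 mmol/l. A difference above 0.5 mmol/l in either direction occurs about 33% of the time. Given an observed imbalance d, the change-score estimate shifts by -(1-r)d with complete data and by -p(1-r)d under the imputation. The last two columns show the absolute shift for d = 0.52.

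| r | Variance ratio, complete | Variance ratio, 25% imputed | 60 adjusted are worth, complete | 60 adjusted are worth, imputed | Shift, complete (mmol/l) | Shift, imputed (mmol/l) |
|---|---|---|---|---|---|---|
| 0.3 | 0.65 | 0.74 | 92 | 81 | 0.36 | 0.27 |
| 0.5 | 0.75 | 0.81 | 80 | 74 | 0.26 | 0.19 |
| 0.7 | 0.85 | 0.89 | 71 | 68 | 0.15 | 0.12 |
| 0.9 | 0.95 | 0.96 | 63 | 62 | 0.05 | 0.04 |

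The columns headed as worth are 60 divided by the variance ratio: the number of unadjusted participants that would give the same precision.

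**Power, complete data.** For an illustrative difference of 1.0 mmol/l at 30 per arm, adding baseline raises power from 37% to 53% (r = 0.3), 49% to 61% (0.5), 71% to 77% (0.7) and 99.1% to 99.3% (0.9).

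**Does diabetes status do the same job?** A simulation of 4,000 trials at 30 per arm assumed half the participants in each cohort, cohort means 2 mmol/l apart and overall SD 2.0. Week-12 glucose depended on baseline glucose alone, a set-up that favours the continuous covariate. Standard errors of the treatment effect (mmol/l):

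| r | Change only | Change + diabetes status | Change + baseline glucose |
|---|---|---|---|
| 0.5 | 0.509 | 0.504 | 0.454 |
| 0.7 | 0.400 | 0.396 | 0.372 |
| 0.9 | 0.229 | 0.229 | 0.226 |

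In this scenario, status recovers little of the loss even when it is always included.

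**The case against.** A reader might infer that a chance baseline difference goes wholly uncorrected and is credited to treatment, or that the result is biased and the trial undersized. The documents do not support this. The change score already subtracts baseline, so only the fraction (1-r) of an imbalance remains. Under randomization the contrast is unbiased on average; the residual is conditional on the imbalance that happens to be drawn. The stated 32 reproduces, and 30 per arm gives ample power for the design difference. At r = 0.5, the complete-data shift of 0.26 mmol/l is 13% of the 2.0 mmol/l target.

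The plan also has a partial response to imbalance in its conditional diabetes-status term. That stands as mitigation, but the term is binary, depends on the observed data, and does not replace the baselines of the secondary outcomes.

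The size is uncertain. Stable differences between the two cohorts would tend to raise r, and at r = 0.9 the gain is only about 5%. The planned imputation shrinks both the gain and the shift, as the table shows.

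Finally, the article is condensed, and the full model may hold terms it does not print. That limits certainty about what will be run. Still, the article gives an explicit covariate list, not a general reference to adjustment. If the full plan includes baseline, the published list needs to be brought into line with it.

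**Conclusion.** The point holds as a free improvement that should be made; it is not a flaw that invalidates the analysis. The test, the estimand and the stated sample size stand. What is lost is precision, together with protection against the particular imbalance this one small trial may draw. Over r from 0.3 to 0.9, adjustment would cut the variance by 35% to 5% with complete data, or by about 26% to 4% with a quarter of week-12 values imputed as no change. These figures rest on the assumed r, on equal SDs of 2.0 mmol/l at both visits, and on drop-out unrelated to baseline. The direction does not depend on the exact r, so long as it is below 1.

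**What to change.** In the Statistical analysis section, prespecify baseline fasting plasma glucose as a covariate in the primary model, and the baseline value of each secondary outcome in that outcome's own model. With baseline in the model, using change or the week-12 value as the response gives the same treatment estimate in a linear model.

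The cost is one clause and one degree of freedom per model, with no new data. Trial status reports recruitment as ongoing, so the change should be fixed and dated before unblinding; adopted after results are seen, it would look discretionary. The argument here does not extend to the other listed terms. In particular, adjusting for percentage weight change is a separate issue.

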### Allocation

Participants will be randomized to the probiotic or placebo group without stratification using computer-generated random numbers (FileMarker Pro). Both participants and study investigators will be blinded to treatment allocation. Participant unblinding will only be requested in a medical emergency, where knowledge of the study treatment is essential for any treatment of the participant. The reason for unblinding will be documented and the study treatment will not be revealed to any member of the study team.

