### Inclusion criteria

Participants are eligible for the study if they meet the following criteria:Aged ≥ 18 yearsBody mass index ≥ 25 kg/m^2^
Have prediabetes or have been diagnosed with type 2 diabetes mellitus within the previous 12 monthsAre treated by diet alone or diet plus metforminAre willing to adhere to the study protocol (no yoghurt, fermented food, dietary supplements, probiotics or prebiotics) for the duration of the study.

The definition of prediabetes is based on the American Diabetes Association guidelines [15] and participants must have: (i) a fasting plasma glucose level between 5.6 mmol/l and 6.9 mmol/l or; (ii) two-hour post-challenge (oral glucose tolerance test) plasma glucose level between 7.8 mmol/l and 11 mmol/l or; (iii) HbA1c between 5.7% and 6.4%.

The criteria for the diagnosis of type 2 diabetes mellitus is based on the American Diabetes Association guidelines [15]. Participants are included in the study if they have been diagnosed with type 2 diabetes mellitus by their general practitioner in the previous 12 months or have: (i) a fasting plasma glucose level ≥ 7.0 mmol/l or; (ii) 2-hour post-challenge (oral glucose tolerance test) plasma glucose level ≥ 11.1 mmol/l or; (iii) an HbA1c ≥ 6.5%.

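### Diabetes cohort enters the model only if an imbalance is found; it should be a fixed covariate, because the conditional rule can cost precision and gains nothing

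*Protocol article*

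**What the plan says.** - **Model.** "Primary and secondary outcomes will be analyzed using generalized linear models" (Protocol article, Statistical analysis).
- **Fixed covariates.** "The following covariates will be added to the model: sex, age and percentage weight change". Neither cohort nor baseline glucose is on this list.
- **Conditional covariate.** "if there is an imbalance between the groups of prediabetes and type 2 diabetes mellitus, this will be included as a covariate" (same section).
- **Allocation.** "Participants will be randomized to the probiotic or placebo group without stratification" (Allocation).
- **Acknowledged heterogeneity.** The Sample size section notes that two cohorts are enrolled and that "owing to the lack of stratification at randomization the variance could be high". Its response is to enlarge the trial to 30 per group.
- **Primary outcome.** The between-group difference in the change in fasting plasma glucose from baseline to 12 weeks (Primary outcome measure).

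A subgroup analysis by prediabetes or type 2 diabetes is also planned. It does not adjust the primary comparison.

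**The concern.** A baseline factor belongs in the model because it predicts the outcome. When it does, adjustment removes between-cohort variation from the residual even if the arms are perfectly balanced. The plan uses a different criterion, observed imbalance, which says nothing about how strongly cohort predicts glucose change.

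Two things follow. The primary model is not settled until the realised allocation is known. And in the many randomizations where the trigger does not fire, the factor that the plan itself singles out as a source of variance stays in the error term. What is at stake is precision in a small trial. The plan pays for heterogeneity with extra participants but makes the cheaper remedy, a covariate, conditional.

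**Working it through.** **1. The plan's own figure.** Inputs from Sample size: difference 2.0 mmol/l, SD 2.0 mmol/l, 80% power, 95% confidence (read as two-sided 0.05).

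n per arm = 2 × (1.960 + 0.842)² × (2.0/2.0)² = 15.7, so 16 per arm and 32 in total. The stated 32 reproduces.

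With 25% drop-out, 32/0.75 = 42.7, so 43. By subtraction, about 60 − 43 = 17 participants are an allowance for higher variance that the plan does not quantify further.

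**2. How often a trigger would fire.** The number with type 2 diabetes in one arm of 30 out of 60 is hypergeometric. The share with type 2 diabetes is not stated, so 20-50% is assumed.

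| Type 2 diabetes among 60 | Arms differ by ≥10 points | by ≥20 points | chi-square p<0.05 |
|---|---|---|---|
| 12 (20%) | 33% | 10% | 2.1% |
| 18 (30%) | 40% | 16% | 4.7% |
| 24 (40%) | 43% | 19% | 6.4% |
| 30 (50%) | 44% | 20% | 7.0% |

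A p<0.05 trigger therefore leaves cohort out in 100 − 7.0 = 93.0% to 100 − 2.1 = 97.9% of randomizations. A 10-point trigger would leave it out in 56-67%.

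**3. What leaving it out costs.** Let d be the cohort gap in the analysed outcome (12-week change), p the share with type 2 diabetes, and 2.0 the within-cohort SD. With 30 per arm:

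- SE without cohort = √[(4 + d²p(1−p)) × 2/30]
- SE with cohort ≈ √[4 × 2/30] = 0.516

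At p = 0.4, p(1−p) = 0.24, so the SE without cohort is:

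- d = 0: √(4.00/15) = 0.516
- d = 1: √(4.24/15) = 0.532
- d = 2: √(4.96/15) = 0.575
- d = 3: √(6.16/15) = 0.641

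**4. Simulation of the rules.** Linear model, 10,000 runs per scenario, N = 60, 24 with type 2 diabetes, within-cohort SD 2.0. The other covariates were not simulated. The simulated spread of the unadjusted estimate agrees with step 3 (0.516, 0.533, 0.574 and 0.640).

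Power for a true effect of 1.5 mmol/l:

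| Rule | d = 0 | d = 1 | d = 2 | d = 3 |
|---|---|---|---|---|
| Always include cohort | 0.81 | 0.81 | 0.80 | 0.81 |
| Only if p<0.05 | 0.81 | 0.79 | 0.73 | 0.64 |
| Only if ≥20 points | 0.81 | 0.79 | 0.74 | 0.67 |
| Only if ≥10 points | 0.81 | 0.80 | 0.76 | 0.71 |

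Type I error, nominal 0.05:

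| Rule | d = 0 | d = 1 | d = 2 | d = 3 |
|---|---|---|---|---|
| Always include cohort | 0.046 | 0.050 | 0.050 | 0.048 |
| Only if p<0.05 | 0.046 | 0.049 | 0.043 | 0.037 |
| Only if ≥20 points | 0.046 | 0.049 | 0.041 | 0.030 |
| Only if ≥10 points | 0.046 | 0.049 | 0.042 | 0.030 |

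The preset rules turn conservative because, when the arms are nearly balanced, the unadjusted model still charges the between-cohort variance to the standard error although little of it affects the contrast.

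**The case against.** **The loss may be small.** The primary outcome is change, and a stable difference in glucose level between cohorts cancels in a change score. Only a difference in 12-week change matters, and the protocol gives none. The eligibility criteria also let the cohorts overlap on fasting glucose: "a fasting plasma glucose level between 5.6 mmol/l and 6.9 mmol/l" is only one of three routes to prediabetes, and type 2 diabetes may be established by other tests or by a general practitioner's diagnosis. The large losses appear only at assumed gaps of 2-3 mmol/l, as large as or larger than the 2.0 mmol/l treatment difference used for sample size. This stands, and it limits how large the harm can be said to be. For the same reason a reader should not size the point from glucose levels. A level gap of 1.5-3 mmol/l with 30-50% type 2 diabetes gives a variance share d²p(1−p)/4 of 12-56%, but that is a share of the variance of level. On the same formula at p = 0.5, gaps in change of 0.5 and 1.0 mmol/l give 1.6% and 6.3%.

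**Type I error.** A reader might infer that the rule lets the analyst choose between two p-values. The article does not support this. The trigger rests on baseline cohort counts, not outcomes, and a preset threshold does not inflate the error. Free choice of the more favourable model would give 0.051, 0.060, 0.068 and 0.077 for gaps of 0 to 3 mmol/l, but that needs a trigger left open. The threshold may be set in an analysis plan that is not shown, so its absence from a condensed article is no finding.

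**The Sample size sentence.** A reader might call it wrong to link variance to unstratified allocation. The wording is loose but defensible: without adjustment for cohort, unstratified allocation does add sampling variance to the treatment contrast through chance imbalance.

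**Meaning of imbalance.** The phrase could refer to unequal cohort sizes rather than unequal arms. The model would still depend on the data.

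None of this defends making inclusion conditional. At zero gap, always adjusting costs nothing visible (0.81 under either rule).

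**Conclusion.** The point holds as a matter of precision. The conditional rule is in the article, allocation is unstratified, the plan itself flags the two cohorts, and nothing else in the document adjusts the primary comparison for them. Whatever threshold is used, the rule can leave a likely prognostic factor out.

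The loss runs from none, if the cohorts change alike, through about 2 points of power at a 1 mmol/l gap, to about 17 points at 3 mmol/l with a p<0.05 trigger. These figures rest on assumed gaps, an assumed 40% with type 2 diabetes and a within-cohort SD of 2.0 mmol/l. The existence of the rule is certain; the size of its consequence is not known from the document. The case for changing it is that fixed adjustment is practically free and protects against the larger losses.

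**What to change.** In Statistical analysis, replace the conditional sentence with:

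*Diabetes cohort at baseline (prediabetes or type 2 diabetes) will be included as a fixed covariate in the primary and secondary models regardless of observed balance.*

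The cost is one sentence and one degree of freedom. Cohort is already recorded for eligibility and for the planned subgroup analysis, and the sample size does not change. The article reports recruitment as ongoing, so at that stage the change could still be made before unblinding. Stratifying the remaining allocations is not needed for this purpose, and the document does not say how many participants remained to be recruited.

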**Methods:**

Sixty adults with a body mass index ≥25 kg/m^2^ with prediabetes or type 2 diabetes mellitus (diagnosed within the previous 12 months) will be enrolled in a double-blind, placebo-controlled pilot study. Participants will be randomized to a multi-species probiotic or placebo for 12 weeks. Both groups will receive lifestyle and nutritional advice. The primary outcome measure is the change between groups in fasting plasma glucose levels from baseline to 12 weeks. Secondary outcome measures include, but are not limited to, the change in lipid profile, systemic inflammation, gut permeability, and faecal microbial and metabolomic profiles. Blood and stool samples are collected at baseline and 12 weeks after treatment.

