A probiotic is a microbiota-based intervention defined as ‘a live microorganism, which, when administered in adequate amounts, confers beneficial health effects on the host’ [2, 8, 9]. A meta-analysis evaluating the effect of probiotics on glycaemia suggests that probiotics can play an important role in the prevention and treatment of type 2 diabetes mellitus [10]. Certain probiotic species have improved insulin sensitivity, inflammatory markers and lipid profiles in obese, type 2 diabetes mellitus and dyslipidaemic subjects [11–13]. However, it is not known whether a combination of probiotic species that have demonstrated beneficial therapeutic effects individually can improve metabolic markers associated with type 2 diabetes mellitus and have an additive effect to standard care. Therefore, we have formulated a novel prescription containing eight probiotic species that belong to the *Lactobacillus*, *Bifidobacterium*, *Streptococcus* and *Saccharomyces* genera to improve glucose metabolism in subjects with prediabetes and early type 2 diabetes mellitus*.* This multi-species probiotic formula has been tested previously in our laboratory using *in-vitro* models with rodent fat and muscle cell lines. The results from these *in-vitro* experiments showed the supernatants collected from the growth media of the probiotic decreased lipid accumulation in 3T3-L1 adipocytes and restored glucose uptake in insulin resistant L6 muscle cells [7]. The formulation and dosage proposed in this study have not been investigated previously in human studies. Therefore, the aim is to test the safety and efficacy of this novel probiotic formulation in adults with prediabetes and early type 2 diabetes mellitus. We hypothesize that a shift in the gut microbiome induced by this multi-species probiotic will decrease metabolic and inflammatory markers and result in improved blood glucose management.

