## Methods

### Design

This pilot study is a single site, randomized, double-blind, placebo-controlled clinical trial conducted at the Charles Perkins Centre Royal Prince Alfred Clinic in Sydney, Australia. Sixty adults with prediabetes or early type 2 diabetes mellitus will be randomized to take either a multi-species probiotic capsule or placebo for 12 weeks. The Standard Protocol Items: Recommendations for Interventional Trials (SPIRIT) was used to elaborate the study protocol (see Additional file 1). Participants’ progression through the trial is presented in Fig. 1 (CONSORT diagram [14]).

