### Intervention and compliance

#### Investigational product

The study coordinator will obtain written informed consent and randomize eligible participants to the multi-species probiotic or placebo. The study product contains either 50 × 10^9^ colony forming units (cfu) of a multi-species probiotic (27 × 10^9^ cfu of *Lactobacillus* spp., 22.5 × 10^9^ cfu of *Bifidobacterium* spp., 450 × 10^6^ cfu of *Streptococcus* spp. and 45 × 10^6^ cfu of *Saccharomyces* spp., patent pending) or 50 mg of the placebo (maltodextrin) per capsule. The probiotic and placebo capsules are opaque white and look and smell identical. Verbal and written instructions on how to take the study product or placebo will be provided at the initial and each review visit. Enrolled participants will be required to:Take two capsules twice per day (20 min before breakfast and dinner) with cold non-carbonated water. The product is not to be mixed or taken with hot drinks or foods, as heat and stomach acids can reduce the stability of the probiotic bacteriaStore the study product in the fridge at 4–6 °CRecord the number of capsules taken each day in the study diaryBring all capsules remaining in the bottle to the next visitAvoid eating or drinking yoghurt, fermented food, dietary supplements (i.e. vitamins, minerals, nutraceuticals, herbal preparations, probiotics, prebiotics or fish oils) and antibiotics (unless recommended by a health professional).

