#### Study product compliance

Capsule counting, at weeks 6 and 12, will be used to assess the participant’s compliance in taking the study product. A record of the date, the visit and the amount of study product dispensed and returned will be documented for each participant. Participants are defined as non-compliant if they have taken less than 80% of the study product on both occasions.

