#### Stool samples

Stool samples will be collected at baseline and 12 weeks using a stool specimen collection kit. This collection kit includes an instruction booklet for the stool sample collection and transportation, ice packs, gloves, a sterile container, sealed plastic pouch, cool box and an AnaeroGen™ Compact sachet, which preserves the microbiological characteristics of the sample for 72 hours. Participants will bring the stool sample to the clinic and the containers will be stored at 4 °C and analyzed by matrix-assisted laser desorption ionization time-of-flight mass spectrometry 24–48 hours after collection. In addition, a 1 g sample will be stored at −80 °C for faecal microbial and metabolite profiling. DNA extraction will be performed using the QIAamp DNA stool kit (Qiagen, Sydney, NSW, Australia). Faecal microbial composition will be identified by sequencing the 16S rRNA using the Ion S5 next-generation sequencing system (Thermo Fisher, Sydney, NSW, Australia). Short-chain fatty acids, secondary bile acids and choline by-products will be measured using gas chromatography-mass spectrometry.

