## Discussion

This randomized trial will assess the efficacy and safety of a multi-species probiotic formulation in the management of prediabetes and type 2 diabetes mellitus metabolic markers. The study outcomes may lead to novel treatments to reduce the metabolic disturbances associated with these disorders. This study will also provide empirical evidence to address currently unresolved issues with the efficacy and safety of probiotics. In designing this clinical study, several key decisions were made to overcome current limitations in the published literature and reduce possible biases.

While focusing on those with prediabetes, subjects with early type 2 diabetes mellitus were included to assess the feasibility of inducing partial or complete remission of type 2 diabetes mellitus. This decision also meant including participants taking metformin as this drug is commonly prescribed early in type 2 diabetes mellitus; it has also been shown to have effects on the microbiome [21, 22]. Furthermore, microbiota-based interventions may reduce gastrointestinal symptoms associated with metformin administration with a consequent improvement in medication compliance [23]. As far as we are aware, the interaction between the gastrointestinal microbiota, probiotics and metformin has not been explored in patients with prediabetes and type 2 diabetes mellitus. Therefore, this study will assess the efficacy and safety of a novel multi-species probiotic and provide preliminary data on its effect on metformin.

Limitations of the study include the short-term impact of the intervention, as subjects will be treated for only 12 weeks. Additionally, the small number of visits during the study can be considered a risk factor for non-compliance. Moreover, it must be remembered this study is investigating the short-term impact of a multi-species probiotic formulation to help improve fasting blood glucose levels. It is known that probiotics do not recolonize the intestinal tract but rather are transient colonizers and that wash-out of administered doses can take from approximately 4–6 weeks, thereby leading to a therapy that may be not be permanent.

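### Week-12 differences between arms in the administered genera may reflect swallowed product; a repeat analysis without those taxa would show whether the rest of the community changed

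*Protocol article*

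**What the plan says.** The Background section sets out a mechanism: "We hypothesize that a shift in the gut microbiome induced by this multi-species probiotic will decrease metabolic and inflammatory markers".

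The sampling and dosing calendar comes from four places in the article:
- Design: participants are "randomized to take either a multi-species probiotic capsule or placebo for 12 weeks".
- Study product compliance: "Capsule counting, at weeks 6 and 12, will be used to assess the participant’s compliance in taking the study product".
- Stool samples: "Stool samples will be collected at baseline and 12 weeks using a stool specimen collection kit". Composition is read by 16S rRNA sequencing.
- Investigational product, on dosing: "Take two capsules twice per day (20 min before breakfast and dinner) with cold non-carbonated water".

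The Statistical analysis section covers alpha and beta diversity and states that "comparisons of genus and species level data will be performed to reveal differences in the microbial composition between the two groups". It then tests relative abundance of taxa between arms, correlates abundance changes with biochemical measurements, and applies a Benjamini–Hochberg adjustment. The administered genera are neither set apart nor said to be included.

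The Discussion adds: "It is known that probiotics do not recolonize the intestinal tract but rather are transient colonizers". It puts wash-out at roughly 4–6 weeks.

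**The concern.** A participant who swallows large numbers of Lactobacillus, Bifidobacterium and Streptococcus up to the time of sampling can be expected to pass some of their DNA in stool. 16S sequencing counts that DNA whether or not anything else in the gut has changed. A between-arm difference in these genera therefore has two possible readings: the product is passing through, or the community has moved. The comparison as described does not separate them.

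The Benjamini–Hochberg step does not help, because a rise in swallowed organisms is a real difference and not a chance finding. Only its interpretation is in doubt.

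The correlations with biochemistry are the most exposed step. Abundance of the administered taxa will track allocation and adherence. If the correlations are run across both arms, which the article does not specify, any effect of the product on glucose, by whatever route, could appear as a correlation with these taxa and be taken as support for the microbiome mechanism.

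**Working it through.** **1. Calendar.** Dosing lasts 12 weeks, with the last capsule count at week 12. Stool is taken at baseline and week 12. The gap between last dosing and the last stool sample is therefore about 0 weeks, against the article's own wash-out of 4–6 weeks. A sample beyond wash-out would fall at about weeks 16–18 (12 + 4 to 12 + 6), and none is described. The abstract's wording, "Blood and stool samples are collected at baseline and 12 weeks after treatment", could be read as after treatment ends, but the Design, Study product compliance and Stool samples sections together point to week 12 of dosing. The schedule figure is not available to settle it.

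**2. Daily intake from the article's figures.** The content is read as per capsule. The four listed components sum to 27 + 22.5 + 0.45 + 0.045 = 49.995 × 10^9 cfu, which matches the stated 50 × 10^9. At four capsules a day:
- Lactobacillus: 4 × 27 × 10^9 = 1.08 × 10^11
- Bifidobacterium: 4 × 22.5 × 10^9 = 9.0 × 10^10
- Streptococcus: 4 × 0.45 × 10^9 = 1.8 × 10^9
- These three together: 1.998 × 10^11, or 99.9% of the total of 1.9998 × 10^11. Saccharomyces is a yeast and is not read by 16S.

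Both arms must avoid yoghurt, fermented food and other probiotics, so the capsule is the main planned difference between arms in intake of such organisms.

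**3. Share of the stool signal (illustration).** Three inputs are assumptions that the article does not give: daily faecal bacterial output T, fraction s of dosed DNA recovered, and a resident Lactobacillus share of 0.1%. With L = 1.08 × 10^11 and C = 1.998 × 10^11:
- Lactobacillus added = L·s / (T + C·s)
- scaling of every other taxon = T / (T + C·s)
- fold-rise in Lactobacillus = (0.001·T + L·s) / (T + C·s) / 0.001

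| T per day | s | Lactobacillus added | Other taxa scaled by | Fold-rise |
|---|---|---|---|---|
| 5 × 10^12 | 100% | 2.08% | 0.962 | 21.7 |
| 5 × 10^12 | 10% | 0.22% | 0.996 | 3.1 |
| 1 × 10^13 | 100% | 1.06% | 0.980 | 11.6 |
| 1 × 10^13 | 10% | 0.11% | 0.998 | 2.1 |
| 3 × 10^13 | 100% | 0.36% | 0.993 | 4.6 |
| 3 × 10^13 | 10% | 0.04% | 0.999 | 1.4 |

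Streptococcus adds at most 1.8 × 10^9 / (5 × 10^12 + 1.998 × 10^11) = 0.035%.

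**4. Wider range.** With T from 10^12 to 10^14 and s from 1% to 100%, the capsule share of reads runs from 0.002% to 16.7%, other taxa are scaled by 1.00 to 0.83, and the Lactobacillus fold-rise runs from 1.01 to 91. The low end is negligible.

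**5. Reading the results.** The fold-rise is approximately 1 + L·s/(0.001·T), so its excess over 1 shrinks roughly in inverse proportion to the assumed resident share. It can be large for a genus that is otherwise rare and modest for a common one. The dilution of everything else is small in the main range: at most 1 − 0.962 = 3.8%. No effect on a diversity index was computed.

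**The case against.** The strongest reply has four parts.

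*The article is silent and does not commit to including these taxa.* Filtering is a pipeline detail that an unseen analysis plan could hold. This stands: a reader might infer that the administered genera certainly enter every comparison, but the text only fails to set them apart. The suggestion is therefore offered as an added analysis and not as a correction of missing detail.

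*On-treatment sampling is legitimate.* It matches the week-12 blood sample, and the Discussion accepts that the effect may not last. This also stands. A reader might infer that the sampling time is itself a design error; the documents do not support that.

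*The hypothesis never says resident community.* It speaks of a shift in the gut microbiome, and enrichment by the dosed organisms could count as part of such a shift. A reader might infer that the mechanistic question cannot be answered at all from these data. That goes too far: taxa are tested individually, so one can see which ones moved, and the faecal metabolites are not capsule DNA.

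*The numbers rest on outside assumptions.* They do, and the range includes no visible effect.

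What remains is narrower. The planned comparison and correlations do not distinguish capsule organisms from change in other organisms, and the article's own statement about transience makes the first reading a live one.

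**Conclusion.** The point holds as a cheap improvement to the analysis of a secondary outcome. Differences between arms in Lactobacillus, Bifidobacterium and Streptococcus at week 12, and their correlations with biochemistry, may reflect swallowed product. The calendar, the dose and the transience statement come from the article. That the administered taxa remain in the comparison is read from the absence of any stated exclusion.

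The size is uncertain. For a genus with an assumed 0.1% resident share, the rise from passage alone is about 1.4-fold to 22-fold in the main range. Other taxa lose at most about 4% of their share, so the effect on them and on diversity is probably small; only the extreme of the wider range (17% dilution) would change that. A reader might infer that any diversity difference would be a capsule artefact, but these figures do not show it. Differences in non-administered taxa are affected only through dilution, and the metabolite outcomes and the primary fasting glucose comparison are not directly affected.

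**What to change.** Keep the all-taxa analysis and add the following, specified before the sequence data are compared by arm:
- Repeat the diversity, taxa and correlation analyses with the administered species removed and relative abundances re-normalised. Where 16S does not resolve the species, remove the genus.
- Report the administered taxa separately as markers of exposure.
- Describe the week-12 result as an on-treatment state, and claim a shift beyond the administered organisms only if the filtered analysis supports it.

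The cost is one extra filtering step on data already collected; no new samples or participants are needed and no sample-size figure changes. The downside is that the filtered analysis cannot show true changes in resident members of the removed genera, including changes the product may induce. For that reason the all-taxa analysis should stay beside it.
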